### Trial design {8}

The trial is a randomised, comparative, open-label, single-centre, phase IV trial, with planned 200 women randomised 1:1 to a single dose of IV FDI or a fixed dose of oral iron ferrous fumarate with ascorbic acid. The randomisation is stratified by Hb value (≥ or < 11.0 g/dL).

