### Outcomes {12}

The primary endpoint of this trial is a Hb ≥11.0 g/dL (≥ 6.8 mmol/L) at all trial visits post-baseline (*T*_3w_, *T*_6w_, *T*_12w_, and *T*_18w)._

The secondary endpoints are Hb ≥ 11.0 g/dL (≥ 6.8 mmol/L) at each follow-up visit, change in Hb and other haematological indices of ID/IDA from baseline to each follow-up visit (e.g. reticulocytes, reticulocyte haemoglobin content (CHr), *s*-ferritin, *s*-transferrin, *s*-iron, hepcidin, and calculated transferrin saturation (TSAT)), incidence of hypophosphatemia (defined as serum [*s*]*-*phosphate < 2 mg/dL) from baseline to each follow-up visit, change in fatigue and quality of life questionnaires from baseline to each follow-up visit, presence of RLS at each follow-up visit, number of participants who receive an additional IV iron isomaltoside dose at *T*_6w_ and/or *T*_12w_, reason for the additional IV iron isomaltoside dose (non-compliance, lack of effect), number of participants receiving RBC transfusions and the number of RBC units per transfused participant from baseline to final subject visit, type and incidence of AEs observed at any time until final subject visit, serious or severe hypersensitivity reaction starting at or after the first dose of randomised treatment, AEs of special interest (constipation, diarrhoea, flatulence, nausea, vomiting, abdominal pain, dyspepsia, dysgeusia, and stool discoloration), number of participants who discontinue from the trial because of lack of response or intolerance of investigational drugs, foetal bradycardia related to infusion of IV iron isomaltoside at or after GA 26, change in biochemical safety parameters from baseline to each follow-up visit, and compliance to treatment: at baseline in the IV group and at *T*_6w_ and *T*_18w_ in the oral group.

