### Sample size {14}

The sample size calculations are based on the primary endpoint: Hb ≥ 11 g/dL (≥ 6.8 mmol/L) at all time points after baseline [1, 5]. The primary endpoint will be estimated by a Kaplan-Meier curve. Participants who drop out during the trial will be accounted for (set as ‘censored’) by the methodology and therefore not addressed specifically in the sample size calculations. It is assumed that 5% and 17.5% of the participants in the FDI and oral treatment groups respectively will have a Hb < 11 g/dL at some point during the trial, corresponding to 95% and 82.5% will have a Hb ≥ 11 g/dL at all post-baseline visits. Using a significance level of 5%, and setting the power to 80%, 100 participants in each treatment group are required in order to detect the assumed difference between FDI and oral iron.

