### Implementation {16c}

The investigators consecutively invited all eligible participants to attend the baseline visit. At the baseline visit, demographics and latest Hb level are entered in the eCRF prior to randomisation. Thereafter, the participant is randomised stratified by Hb value and proceeds to the allocated treatment.

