## Statistical methods

### Statistical methods for primary and secondary outcomes {20a}

Time to Hb < 11 g/dL and proportion of participants with correction of anaemia (Hb ≥ 11.0 g/dL) at *T*_3w_, *T*_6w_, and *T*_12w_ will be estimated by a Kaplan-Meier curve using scheduled visits. Based on the Kaplan-Meier curve, the proportion of participants who have met the primary endpoint (achievement/maintenance of Hb ≥ 11 g/dL at all post-baseline visits) at *T*_18w_ will be estimated and compared between the treatment groups.

The primary endpoint analysis will be performed for the intention-to-treat analysis set and will be repeated for the full analysis set and per protocol analysis sets.

As sensitivity, the risk difference will be used to compare the proportion of participants with Hb ≥ 11 g/dL at all post-baseline visits. Risk difference and the associated 95% Newcombe CI and *p* value will be calculated, adjusting for strata (Hb </≥ 11 g/dL at inclusion) using the Cochran-Mantel-Haenszel method. In this analysis, participants who do not complete the study period will be set as failures.

The change in Hb and biochemical safety parameters from baseline to *T*_3w_, *T*_6w_, *T*_12w_, and *T*_18w_ will be analysed using a restricted maximum likelihood-based mixed model for repeated measures approach.

The proportion of participants who (a) receive an additional IV FDI dose, (b) receive allogenic RBC transfusions, (c) discontinue from the trial because of lack of response or intolerance of investigational drugs, and (d) develop hypophosphatemia will be compared between the treatment groups by Fisher’s exact test.

The number of units of RBC transfused per transfused participant from baseline to final subject visit will be compared between the treatment groups by an analysis of variance or Wilcoxon test.

For participants in the oral iron group, AEs with onset at/after the time of first additional IV iron isomaltoside dose will be excluded from the main AE summaries. In addition, displays of all AEs per overall treatment group will be produced, as well as summaries and participant listings of AEs occurring at/after the time of first additional IV iron isomaltoside dose.

Medical record follow-up will be tabulated by descriptive statistics.

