### Methods in analysis to handle protocol non-adherence and any statistical methods to handle missing data {20c}

The intention-to-treat (ITT) analysis set will include all subjects as randomised. The per protocol (PP) analysis set will include all subjects who do not have any major protocol or GCP deviation of clinical or statistical significance. Non-compliance, i.e. treatment dose outside the 80–120% range within the first 6 weeks of treatment, is considered a major protocol deviation.

All participants in the intention-to-treat analysis set with post-baseline Hb data will be included with their observed data. Participants without post-baseline Hb values will have change from baseline set to 0 at the first post-baseline visit. The model will include the fixed, categorical effects of treatment, week, and treatment-by-week interaction as well as the continuous, fixed covariates of baseline Hb value and baseline Hb-by-week interaction. Similar analyses will be performed for the other haematological indices (reticulocytes etc.), change in fatigue, QoL, and RLS.

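### As described, the primary T18w comparison uses neither continuous baseline Hb nor the randomisation stratum, and so gives up a modest amount of precision

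*Protocol article*

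**What the plan says.** All references are to the protocol article.

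- **Endpoint (Outcomes {12}).** "The primary endpoint of this trial is a Hb ≥11.0 g/dL (≥ 6.8 mmol/L) at all trial visits post-baseline", at 3, 6, 12 and 18 weeks.
- **Primary analysis (Statistical methods {20a}).** A Kaplan-Meier curve of time to Hb below 11 g/dL. "Based on the Kaplan-Meier curve, the proportion of participants who have met the primary endpoint" at T18w is then compared between groups. No test, covariate or stratum is named.
- **Sensitivity analysis (same section).** A risk difference adjusted by Cochran-Mantel-Haenszel for the two-level Hb split at 11 g/dL, with non-completers counted as failures.
- **Secondary model (section {20c}).** The repeated-measures model for change in Hb includes the "continuous, fixed covariates of baseline Hb value and baseline Hb-by-week interaction".
- **Availability of baseline Hb.** Trial design {8} stratifies randomisation at Hb 11.0 g/dL. Under Implementation {16c}, "demographics and latest Hb level are entered in the eCRF prior to randomisation".
- **Sample size {14}.** "It is assumed that 5% and 17.5% of the participants in the FDI and oral treatment groups respectively" fall below 11 g/dL at some point. "Using a significance level of 5%, and setting the power to 80%, 100 participants in each treatment group are required". Dropout is treated as censoring, handled "by the methodology and therefore not addressed specifically in the sample size calculations".

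**The concern.** Failure means that Hb falls below a fixed threshold, so a woman's starting distance from that threshold should help to predict it. The Discussion notes that Hb falls physiologically in the second and third trimesters, which leaves women who start near 11 g/dL less room. The documents never state the strength of this association, but it is a reasonable inference, and stratifying on Hb suggests the planners expected one.

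The two-level split captures little of it. The Discussion calls IDA rare at this stage, so most women should fall in the class at or above 11 g/dL, where 11.1 and 13.0 count alike.

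Two things are at stake. Information already collected is left out of the primary estimate. And if allocation is balanced on Hb but the analysis ignores this, the usual standard error is too large and the test conservative. The design has little slack: about 5 + 17.5 = 22.5 failures are expected, planned power is just above 80%, and there is no allowance for dropout.

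**Working it through.** **1. The plan's own figure.** Inputs from Sample size {14}: 5% and 17.5% failures, alpha 5% (taken as two-sided), power 80%. The mean rate is 0.1125. With pooled variance under the null and no continuity correction:

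n = [1.960 × √(2 × 0.1125 × 0.8875) + 0.8416 × √(0.05 × 0.95 + 0.175 × 0.825)]² / 0.125²
= [0.8758 + 0.3687]² / 0.015625 = 99.1, so 100 per arm.

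Power at 100 per arm: z = (0.125 × √100 − 0.8758) / 0.4380 = 0.854, giving 80.3%. The stated number reproduces. It is an unadjusted two-proportion calculation.

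**2. Effect of adjustment under the stratified design.** Simulation of 200 women, 3,000 trials per setting, 1:1 allocation stratified at the 11 g/dL cut, failure rates 5% and 17.5%, no censoring (so the Kaplan-Meier difference equals the simple risk difference). Three analyses were compared: the unadjusted risk difference; logistic standardisation on the two-level stratum; and logistic standardisation on continuous baseline Hb. The last two use influence-function standard errors.

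Two inputs are assumptions because the documents do not give them: the log-odds ratio of failure per SD of baseline Hb (0.5 to 2, AUC about 0.64 to 0.88), and the share of women below 11 g/dL (5% or 15%).

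| Log-OR per SD | Share <11 | Variance ratio, stratum | Variance ratio, continuous | Power, unadjusted | Power, stratum | Power, continuous |
|---|---|---|---|---|---|---|
| 0.5 | 5% | 1.001 | 0.987 | 83.3% | 83.4% | 83.9% |
| 0.5 | 15% | 1.000 | 0.993 | 82.9% | 83.2% | 83.7% |
| 1.0 | 5% | 0.999 | 0.950 | 84.2% | 85.0% | 86.7% |
| 1.0 | 15% | 1.001 | 0.967 | 82.3% | 83.9% | 85.7% |
| 1.5 | 5% | 0.997 | 0.912 | 83.2% | 85.7% | 88.7% |
| 1.5 | 15% | 0.996 | 0.939 | 83.6% | 87.0% | 89.5% |
| 2.0 | 5% | 0.994 | 0.861 | 85.4% | 88.9% | 92.6% |
| 2.0 | 15% | 1.001 | 0.920 | 85.7% | 90.6% | 93.0% |

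Variance ratios are against the true (simulated) variance of the unadjusted estimate.

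**3. Second parameterisation.** With baseline Hb correlated 0.4 to 0.8 with the lowest follow-up Hb (again assumed) and the same 5% or 15% below 11 g/dL, the variance ratio was 0.84-0.98. Power was 82-86% unadjusted, 82-93% with the stratum only, and 84-95% with continuous baseline Hb.

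**4. Where the power comes from.** In the table, continuous adjustment adds 0.6 to 7.3 points over unadjusted (83.9 − 83.3; 93.0 − 85.7). The stratum alone adds 0.1 to 4.9 points (83.4 − 83.3; 90.6 − 85.7), although its variance ratio stays at 0.99-1.00. So the stratum corrects the standard error without sharpening the estimate, and only the continuous value sharpens it.

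**5. Type I error (11.25% in both arms).** With continuous adjustment it was 4.7-5.8% in the table's settings and 4.4-5.5% in the correlation settings. The unadjusted test fell to 2.6-3.7% at a log-OR of 2.0, which shows the conservatism.

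**6. In numbers of women.** A variance ratio of 0.99 is worth 1/0.99 = 1.01 times as many women; 0.84 is worth 1/0.84 = 1.19 times. At best this is the precision of about 119 per arm instead of 100.

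**The case against.** The strongest reply is that nothing here is wrong. An unadjusted comparison in a randomised trial is valid, the sample size was calculated for one, and the simulated unadjusted power exceeds 80%. The article names no test for the Kaplan-Meier comparison, and an analysis plan not shown may add a covariate. Adjusting a change-from-baseline model is routine and does not show that the sponsor thought it useful for a rare binary endpoint. The sensitivity analysis already adjusts for the stratum. Enrolment closed on 28 February 2020 and the data analysts are not blinded, so a late change to the primary analysis carries a credibility risk.

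Most of this stands, and it limits the point to efficiency. It does not remove the point: the article names covariates for the sensitivity and secondary analyses and none for the primary, and the stratum-adjusted sensitivity analysis leaves the variance of the estimate practically unchanged.

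Four stronger readings are tempting and not supported:

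- **That the primary result would be biased or the trial under-sized.** Neither follows; step 1 reproduces the planned number.
- **That the gain is very large.** Setting the adjusted standard error against the usual unadjusted formula suggests a drop of up to 17%, worth 1/0.83² = 1.45 times as many women. Part of that is the formula overstating the error under stratified allocation: at correlation 0.8 it gives 0.043 against a true SD of 0.038-0.040.
- **That the gains under simple randomisation apply.** Those variance reductions are 3-23%, but this trial stratifies.
- **That adjustment repairs dependent censoring.** In principle, censoring then needs to be independent only given baseline Hb. No dropout rate is given and no simulation included dropout, so this benefit has not been shown.

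**Conclusion.** The point holds as a modest loss of precision. As described, the primary comparison leaves out a baseline value that is collected and used elsewhere in the same plan. Under the stratified design, adjusting for it lowers the true variance of the risk difference by roughly 1-16% and adds about 1-10 points of power, of which the stratum alone recovers about 0-6. The gain is negligible if baseline Hb predicts weakly and useful if it predicts moderately or strongly. These ranges rest on assumed prognostic strength (correlation 0.4-0.8, or log-OR 0.5-2 per SD), on 5-15% of women below 11 g/dL, and on no censoring. The change is worth making; the trial remains valid without it.

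**What to change.** Before database lock, pre-specify that the primary estimate remains the marginal difference in the T18w proportion with Hb at or above 11 g/dL at all visits, estimated with adjustment for continuous baseline Hb and the randomisation stratum. Suitable methods are a covariate-augmented (influence-function) Kaplan-Meier estimator or logistic standardisation, with robust or bootstrap standard errors. State which pre-treatment Hb value is the covariate. A conditional hazard or odds ratio would change the estimand and should not replace the risk difference.

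Do not use Firth-penalised predicted probabilities without an intercept correction. For true rates of 5% and 17.5%, a Firth-penalised visit-by-visit logistic model gave 5.8-6.2% and 17.8-19.1%, and a single-outcome version gave 5.3-5.5% for a true 5%. Keep a penalty only as a fallback for separation.

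Retain the unadjusted Kaplan-Meier comparison as the figure and a supportive analysis. If the analysis plan already adjusts, a sentence saying so is enough.

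The cost is analysis text and no new data. The downsides are a working model in the primary analysis with only about 22 expected events, and the need to document that the change was made before any comparative look at the data, since the analysts are unblinded.

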## Methods: participants, interventions, and outcomes

### Study setting {9}

The trial is being conducted at the Department of Obstetrics and Gynecology at Copenhagen University Hospital, Amager-Hvidovre Hospital, which is a tertiary hospital with 7000–8000 yearly deliveries.

Healthy women who wish to participate and fulfil the inclusion criteria are enrolled at gestational age (GA) 14 + 0–21 + 0. The duration for each participant is approximately 18 weeks and involves four follow-up visits by a trial investigator at the Amager-Hvidovre Hospital.

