Specific explorative endpoints registered between final subject visit up until 7 days postpartum will be extracted from medical records: incidence of maternal antepartum haemorrhage, thromboembolic events, gestational diabetes mellitus, gestational hypertensive disorders, blood transfusions, prolonged labour, length of labour, oxytocin use, assisted delivery, unplanned caesarean section, postpartum haemorrhage, maternal blood loss at labour (ml), length of maternal and neonatal hospital admission, maternal death, incidence of intrauterine growth retardation, preterm birth, ante- or postnatal asphyxia, low birthweight, neonatal infection, neonatal anaemia, required paediatric assistance, admission to neonatal ward, congenital malformations, foetal or neonatal death, GA at delivery, date of delivery and birthweight.

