### Participant timeline {13}

The participants will attend the baseline visit and 4 follow-up visits: *T*_3w_ 3 weeks (± 2 days), *T*_6w_ 6 weeks (± 3 days), *T*_12w_ 12 weeks (± 1 week), and *T*_18w_ 18 weeks (± 1 week) from baseline (see Figs. 1 and 2).

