This trial stands out from other trials regarding the rather strict policy on the gestational age time window for the five trial visits, which we consider a great strength in our study design. We thereby acknowledge that pregnancy is a state with major haemodynamic, hormonal, and physiological changes. We know that haemoglobin drops in 2nd/3rd trimester as part of a physiological process which prepares the pregnant woman for the blood loss associated with delivery [44]. Also, pregnancy symptoms such as fatigue and nausea are more common in 1st trimester and tend to subside in 2nd trimester [45, 46]. By recruiting pregnant women who are all at approximately the same GA at inclusion and thereby also at the follow-up visits, we ensure that the participants are at the same physiological stages at the respective visits. We hypothesise that this will make both the laboratory and clinical result more homogeneous between the treatment groups in that all data is equally affected by the physiological deviations during a pregnancy.

We consider the evaluation of clinically relevant outcomes as a strength in our trial, as these outcomes are very important to investigate. Optimally, we would have used a tool that has been validated in this specific population (European iron-deficient/anaemic pregnant women), which could detect differences in symptoms of ID/IDA while accounting for pregnancy. However, such a tool that fulfils all these criteria does not exist. A recent review illustrates how sparse clinical outcome reporting generally is in trials on perinatal IDA [47].

We chose two self-administered questionnaires in the official Danish versions: FACIT-fatigue and SF-12 in their unedited form (copyright protected). Permission to use the questionnaires has been obtained from the official websites. Both questionnaires are validated in a broader population. This is a limitation in our trial.

We chose the FACIT-fatigue questionnaire because fatigue is considered the most common symptom of anaemia. The questionnaire contains questions that seem appropriate for a pregnant woman and is simple, short, and manageable.

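### Timing visits from baseline puts the last one anywhere from GA 31+0 to 40+0, so the sensitivity analysis scores birth before it as failure and the stated equal-GA comparability does not hold

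*Protocol article*

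**What the plan says.** All references are to the Protocol article.

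- **Enrolment.** Study setting {9}: women "are enrolled at gestational age (GA) 14 + 0–21 + 0". Eligibility {10} gives the same window.
- **Visits.** Participant timeline {13} counts every visit from baseline: 3 weeks (± 2 days), 6 weeks (± 3 days), 12 weeks (± 1 week) and "18 weeks (± 1 week) from baseline". No section ties a visit to a gestational age.
- **Endpoint.** Outcomes {12}: "The primary endpoint of this trial is a Hb ≥11.0 g/dL (≥ 6.8 mmol/L) at all trial visits post-baseline", that is, at 3, 6, 12 and 18 weeks.
- **Primary analysis.** A Kaplan-Meier estimate. Sample size {14}: "Participants who drop out during the trial will be accounted for (set as ‘censored’) by the methodology".
- **Sensitivity analysis.** Section {20a} gives a risk difference with Newcombe interval, stratified by Cochran-Mantel-Haenszel. "In this analysis, participants who do not complete the study period will be set as failures".
- **Repeated-measures model.** Section {20c} lists treatment, week, treatment-by-week, baseline Hb and baseline Hb-by-week. Randomisation is stratified by Hb only (section {8}).
- **Comparability claim.** The Discussion calls the gestational window for the visits strict and a strength: "By recruiting pregnant women who are all at approximately the same GA at inclusion and thereby also at the follow-up visits", the trial is said to ensure that participants share the same physiological stage at each visit. The same paragraph says Hb falls in the second and third trimesters.

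**The concern.** A schedule that starts at randomisation carries the whole enrolment window forward to every visit. Two consequences follow.

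**(a) Birth scored as anaemia.** Late enrollers reach the 18-week visit close to term, and some may have delivered. The endpoint concerns Hb alone, yet the sensitivity rule turns a delivery into a failure. Births are foreseeable in this trial, and the article does not mention them separately from other non-completion. This is also the only alternative handling of missing data stated for the primary endpoint. If it loses significance because of deliveries, it will cast doubt on a primary result that may be sound.

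**(b) A design strength that the dates do not support.** If Hb depends on gestational age, as the Discussion says, then women measured at the same nominal visit but weeks apart in gestation are not at the same stage. The listed model terms do not account for this.

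**Working it through.** **Step 1. Gestational age at each visit.** Lowest GA = 14+0 + visit week − tolerance; highest = 21+0 + visit week + tolerance.

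| Visit | Without tolerance | With tolerance | Spread with tolerance |
|---|---|---|---|
| 3 weeks | 17+0 to 24+0 | 16+5 to 24+2 | 53 days |
| 6 weeks | 20+0 to 27+0 | 19+4 to 27+3 | 55 days |
| 12 weeks | 26+0 to 33+0 | 25+0 to 34+0 | 63 days |
| 18 weeks | 32+0 to 39+0 | 31+0 to 40+0 | 63 days |

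The spread is 7 weeks from enrolment alone and up to 9 with the tolerances. Even 7 weeks exceeds the longest gap between consecutive follow-up visits (6 weeks). One woman's 12-week visit (up to 34+0) can therefore come later in gestation than another's 18-week visit (from 31+0).

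**Step 2. Who is exposed to birth before the last visit.** Anyone enrolled after 19+0 has her nominal 18-week visit after 37+0. If enrolment were uniform over the window (an assumption), that is (21 − 19)/7 = 29% of women. The article gives neither the enrolment distribution nor a birth distribution, so the share who actually deliver first is unknown.

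**Step 3. Reproduce the stated sample size.** Inputs from Sample size {14}: failure 5% v 17.5%, alpha 5% (taken as two-sided), power 80%. Pooled mean p̄ = 0.1125.

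n = [1.960·√(2p̄(1−p̄)) + 0.842·√(p₁q₁ + p₂q₂)]² / (p₂−p₁)²

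= [1.960 × 0.4469 + 0.842 × 0.4380]² / 0.125² = 1.549 / 0.015625 = 99.1, so 100 per arm, as stated.

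Power at 100 per arm = Φ[(0.125 × 10 − 0.8758) / 0.4380] = Φ(0.854) = 80.3%.

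**Step 4. Score births as failures.** Let b be the share per arm, unrelated to Hb status, who deliver before the last visit. Each failure rate becomes f = p + b(1 − p), and the risk difference shrinks by the factor (1 − b). For b = 5%: f₁ = 0.05 + 0.05 × 0.95 = 0.0975 and f₂ = 0.175 + 0.05 × 0.825 = 0.2163. Power = Φ[(1.1875 − 1.0081) / 0.5074] = Φ(0.354) = 63.8%.

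| b (assumed) | Failure, IV v oral | Risk difference (points) | Power, 100 per arm |
|---|---|---|---|
| 0 | 5.0% v 17.5% | 12.5 | 80% |
| 2% | 6.9% v 19.2% | 12.3 | 73% |
| 5% | 9.8% v 21.6% | 11.9 | 64% |
| 10% | 14.5% v 25.8% | 11.3 | 51% |

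The difference itself moves little. Much of the power loss comes from the larger variance once both rates move away from zero.

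**Step 5. Set the comparability claim beside the model.** The Discussion says that Hb falls in the second and third trimesters, so GA is prognostic by its own account. Step 1 shows that GA varies by 7 to 9 weeks within a visit. The model terms in {20c} include baseline Hb and its interaction with week, but nothing for GA.

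**The case against.** **The rule touches a secondary check only.** A reader might infer that births count as anaemia failures in the main result. They do not: the failure rule is confined to the sensitivity analysis, and the Kaplan-Meier analysis censors dropouts. Nor was the trial powered on the sensitivity analysis, and with equal birth shares the rule favours neither arm. All of this stands and limits the point.

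**The rule may be a deliberate conservative bound.** Judging these women on earlier visits credits them without the 18-week Hb that the endpoint requires. That is fair, and it is a reason to show both versions. It is not a reason to merge delivery with every other cause of non-completion.

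**Delivery might not end participation.** The article does not say. But the exploratory endpoints run from the final visit to 7 days postpartum, which implies that the final visit is expected before birth.

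**Randomisation balances GA.** It does so in expectation, and the Discussion writes of only approximate equality. A reader might infer bias between the arms, or that the primary comparison needs GA adjustment; the documents support neither. The claim to ensure a common stage still fails. Adding GA improves precision rather than correcting an error, and an analysis plan not shown here may go further than the terms listed.

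**Complications.** Section {12} says "Specific explorative endpoints registered between final subject visit up until 7 days postpartum will be extracted from medical records". A reader might infer that earlier events are lost. The same section collects adverse events up to the final visit, and transfusions from baseline, so that inference is not supported.

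**Conclusion.** The point holds in limited form. The dates are certain: the last visit spans GA 31+0 to 40+0 and the 12-week visit 25+0 to 34+0.

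Under the literal rule, birth before the last visit becomes a failure in the sensitivity risk difference, and only there. For assumed birth shares of 2% to 10% per arm, the risk difference falls from 12.5 to between 12.3 and 11.3 points, and power from 80% to between about 73% and 51%. These figures rest on equal birth shares in the two arms, births unrelated to Hb status, the article's assumed failure rates, and an unstratified two-proportion approximation. The direction is firm; the size is not, because the article gives no birth share.

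The statement that women are at the same physiological stage at each visit is contradicted by the schedule. Its cost is noise and uncorrected chance imbalance in the repeated-measures contrasts. The article says only that Hb falls in later pregnancy, so no argument should be built on a later recovery. The primary result and the stated sample size are untouched.

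**What to change.** 1. **Sensitivity analysis.** Record birth before the 18-week visit as its own reason for non-completion. Judge these women on their antenatal visits up to delivery, and keep failure for other non-completion. Show the present all-failure version alongside as the conservative bound. Cost: analysis wording and one coded reason. Small downside: these women are classified without an 18-week Hb.
2. **Repeated-measures models.** Add GA at randomisation and GA-by-week for Hb and the other indices. GA must already be known to confirm eligibility, so this needs no new data.
3. **Discussion.** Replace the claim of a common physiological stage with the actual GA range at each visit.

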### Criteria for discontinuing or modifying allocated interventions {11b}

If the participant has IDA at *T*_6w_ or *T*_12w_ defined as Hb < 11 g/dL and *s-*ferritin < 30 μg/L, an additional dose of IV iron isomaltoside is allowed in both groups (not at *T*_18w_ due to lack of AE monitoring). The maximum cumulative dose is set to 2000 mg for the individual participant.

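### The need for an additional IV dose is compared by an unstratified Fisher's exact test although randomisation is stratified at the same Hb cut; a stratified test would be more efficient at no cost

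*Protocol article*

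**What the plan says.** Trial design {8}: "The randomisation is stratified by Hb value", with the cut at 11.0 g/dL.

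Statistical methods {20a} treats this stratum in two ways:

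- The sensitivity analysis of the primary endpoint gives a risk difference with a 95% Newcombe CI and p value, "adjusting for strata (Hb </≥ 11 g/dL at inclusion) using the Cochran-Mantel-Haenszel method".
- Four secondary proportions (additional IV dose, red cell transfusion, discontinuation for lack of response or intolerance, hypophosphatemia) "will be compared between the treatment groups by Fisher’s exact test". No stratification is mentioned.

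Section {11b} sets the condition for the additional dose. It begins "If the participant has IDA at" and names the 6- and 12-week visits, with IDA meaning Hb below 11 g/dL and ferritin below 30 μg/L. Objectives {7} lists the need for an additional IV dose or transfusion as secondary objective (iv).

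**The concern.** An analysis normally reflects the stratification used in the randomisation, above all when the stratum is likely to predict the outcome. For the additional dose there is a reason in the protocol to expect that. Every woman enters with ferritin below 30 μg/L, so a woman in the low-Hb stratum already meets both parts of the additional-dose condition at entry. An unstratified test leaves that predictable variation in the comparison. The exact test is conservative in its own right at this sample size.

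At stake is the reading of a stated secondary objective. A non-significant Fisher result could be taken as no difference in the need for further IV iron when a design-matched analysis of the same data would show one. Fisher's test also gives no stratum-adjusted effect estimate, which the plan already produces for the primary sensitivity analysis.

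**Working it through.** **1. The plan's own figure.** Inputs from Sample size {14}: 5% v 17.5%, significance level 5%, power 80%, 100 per group. With pooled variance, two-sided, no continuity correction:

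n = [1.960·√(2·0.1125·0.8875) + 0.842·√(0.05·0.95 + 0.175·0.825)]² / 0.125² = (0.876 + 0.369)² / 0.015625 ≈ 99.1, rounded up to 100.

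The stated size reproduces, with a power of 80.3% by the same approximation. It concerns the primary endpoint only.

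**2. Fisher's true size.** Exact enumeration at 100 per arm, nominal two-sided 5%, no stratum effect:

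| Common event rate | Fisher | Uncorrected chi-square |
|---|---|---|
| 1% | 0.04% | 1.4% |
| 2% | 0.5% | 4.0% |
| 5% | 2.1% | 4.4% |
| 10% | 2.9% | 5.2% |
| 20% | 3.3% | 5.1% |

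With a strongly prognostic stratum (odds ratio 20), Fisher's size falls to 1.2–1.6% at a 5% rate and 1.3–1.7% at a 10% rate. CMH stays near 5%.

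**3. Power, split by cause.** The CMH statistic, without continuity correction, is [Σ(a_k − n_1k·m_k/N_k)]² / Σ[n_1k·n_2k·m_k·(N_k − m_k) / (N_k²(N_k − 1))]. Here a_k is the number of events in one arm of stratum k, m_k the events in both arms, n_1k and n_2k the arm sizes and N_k their sum. Chi-square minus Fisher is the cost of discreteness. CMH minus chi-square is the cost of ignoring the stratum.

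Assumptions, none of them in the protocol: overall rates of 17.5% v 5% carried over from the primary endpoint, the size of the low-Hb stratum, and the odds ratio (OR) linking stratum to outcome. Simulated, 100 per arm:

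| Stratum OR (low-Hb women per arm) | Fisher | Chi-square | CMH | Discreteness | Stratum | Total |
|---|---|---|---|---|---|---|
| 1 (30) | 76.2% | 82.9% | 82.9% | 6.7 | 0 | 6.7 |
| 5 (20) | 76.9% | 83.9% | 84.9% | 7.0 | 1.0 | 8.0 |
| 10 (20) | 77.9% | 84.9% | 87.6% | 7.0 | 2.7 | 9.7 |
| 20 (20) | 79.1% | 86.1% | 90.6% | 7.0 | 4.5 | 11.5 |

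A separate case assumes 10 low-Hb women per arm with risks of 67% v 32%, and 12% v 2% in the rest. Overall this is 0.1·67 + 0.9·12 = 17.5% v 0.1·32 + 0.9·2 = 5.0%. Power is 78.1% for Fisher, 85.3% for chi-square and 89.6% for CMH. So 7.2 points are due to discreteness and 4.3 to the stratum. These risks imply stratum odds ratios of (67/33)/(12/88) ≈ 15 in the oral group and (32/68)/(2/98) ≈ 23 in the IV group.

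**4. Other rates.** Over stratum odds ratios of 1 to 20, CMH gains about 10 to 18 points on Fisher at 5% v 15% and at 2% v 10%, and about 5 to 12.5 at 10% v 25%. The stratum's share stays between 0 and about 7 points throughout, and the top of that range needs an odds ratio near 20.

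**The case against.** The case for leaving the plan alone has weight.

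- **Fisher's test is valid.** Its type I error stays at or below 5%, and it is a reasonable prespecified choice for a list of possibly sparse outcomes. Power is set only for the primary endpoint, so no power claim is broken. This stands.
- **CMH is named only for a sensitivity analysis of another endpoint.** Using Fisher elsewhere is an inconsistency, not a contradiction. This stands too.
- **The rates are borrowed.** The 17.5% v 5% refers to Hb below 11 g/dL at any of four visits. The additional dose also needs low ferritin, can be given only at 6 or 12 weeks, and is permitted rather than required. Its rate could be quite different. The low-Hb stratum may also be small, since the Discussion calls IDA rare early in pregnancy.
- **Stratified versions might be left to an analysis plan that is not shown.** This does not dispose of the point, because the article names the test.

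Two stronger readings are tempting. A reader might infer that ignoring the stratum is what makes the test conservative and accounts for most of the lost power. The calculations do not support that: discreteness accounts for about 7 points, and the stratum for 0 to 5, at the documented rates. A reader might also extend the argument to all four proportions. Nothing in the protocol links baseline Hb to hypophosphatemia or to discontinuation for intolerance. For transfusion, women already meeting transfusion criteria are excluded, so few events are plausible and an exact method is sensible.

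**Conclusion.** The point holds as a minor matter of efficiency and consistency, chiefly for the additional-dose endpoint. At 100 per arm and assumed rates of 17.5% v 5%, unstratified Fisher loses about 7 to 12 points of power against stratified CMH: about 7 from discreteness and 0 to 5 from ignoring the stratum. The result rests on borrowed rates, an assumed stratum size and an assumed strength of association. Larger losses appear at lower rates, but no particular figure beyond this range can be attributed to the trial, because the protocol gives no rates for the endpoint. The primary analysis, the stated sample size and type I error control are unaffected.

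**What to change.** Analyse the proportion receiving an additional IV dose by the Cochran-Mantel-Haenszel method stratified by the randomisation stratum (Hb below v at or above 11.0 g/dL). Report a stratified risk difference with its 95% CI, as already specified for the primary sensitivity analysis. For consistency the same may be done for the other three proportions, keeping an exact test, preferably stratified, where events are very few, as may be so for transfusion.

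The cost is a change of wording in the analysis section. The Hb value used for stratification is entered in the eCRF before randomisation, and the method is already in the plan. No extra data or participants are needed.
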